# A nurse-led health coaching intervention for stroke survivors and their family caregivers in hospital to home transition care in Chongqing, China: a study protocol for a randomized controlled trial

**DOI:** 10.1186/s13063-020-4156-z

**Published:** 2020-03-04

**Keywords:** Stroke, Stroke survivors, Caregivers, Transitional care, Health coaching, Self-efficacy, Quality of life, Randomized controlled trial

## Abstract

**Background:**

Hospital to home transition care is a most stressful period for stroke survivors and their caregivers to learn self-management of stroke-related health conditions and to engage in rehabilitation. Health coaching has been identified as a strategy to enhance self-management of poststroke care at home. However, interventions in this field that are informed by a health coaching framework are scarce. This study will address a gap in research by testing the hypothesis that a nurse-led health coaching intervention can improve health outcomes for stroke survivors and their family caregivers in hospital to home transition care.

**Methods:**

This is a single-blind, two-arm parallel randomized controlled trial of a nurse-led health coaching program versus routine care situated in two tertiary hospitals in Chongqing, China. Stroke survivors and their primary family caregivers will be recruited together as “participant dyads”, and the estimated sample size is 140 (70 in each group). The intervention includes a 12-week nurse-led health coaching program in hospital to home transition care commencing at discharge from the hospital. The primary outcome is changes in self-efficacy of stroke survivors at 12 weeks from the baseline. The secondary outcomes are changes in stroke survivors’ and quality of life, functional ability, stroke-related knowledge, the number of adverse events, and unplanned hospital admissions, and caregivers’ self-efficacy and caregiver-related burden at 12 weeks from the baseline. The outcomes will be measured at 12 weeks and 24 weeks from the baseline.

**Discussion:**

This study will examine the effect of nurse-led health coaching on hospital to home transition care for stroke survivors and their caregivers. It is anticipated that findings from this trial will provide research evidence to inform policy, and resource and practice development to improve hospital to home transition care for stroke survivors and their caregivers.

**Trial registration:**

The Australian New Zealand Clinical Trials Registry (ANZCTR): ACTRN12619000321145. Registered on 1 March 2019.

## Background

Stroke contributed to 5.9 million deaths and 102 million severe adult disabilities globally in 2010 [1]. Up to 70% of stroke deaths and 78% of stroke associated disability-adjusted life-years (DALYs) lost occur in low- and middle-income countries (LMICs) including China [1]. In China, health loss is mainly caused by stroke, and the morbidity and mortality rates of stroke show an increase over the past 20 years [2]. It is estimated that there are two million new-onset stroke survivors each year in China, making this the second highest incidence of stroke in the world [3]. Of stroke survivors, 75% lose the ability to work, 40% have severe disability and 25%–33% suffer a second-time stroke [4]. Hospital to home transition is viewed as the most challenging period of time for stroke survivors and their family caregivers to adapt self-care at home while engaging in rehabilitation to gain full potential of functional ability and social integration [3, 5, 6]. However, transition care services are largely underdeveloped in most LMICs including China [7, 8]. About 80% of stroke survivors have to discharge to home for later physical and functional rehabilitation due to deficient rehabilitation centers and nursing homes in China [9–11]. Family caregivers play a crucial role in assisting stroke survivors in self-care and rehabilitation during hospital to home transition [12, 13]. However, they usually received little preparation for their caregivers’ role. It is reported that a lack of support for caregivers is associated with physical and psychological stress, caregiving burden and a low level of quality of life [13–16]. Transition care interventions therefore need to consider support for caregivers. This study addresses a gap in research by implementing and evaluating an evidence-based health coaching intervention for stroke survivors and their family caregivers in hospital to home transition in Chongqing, China.

Maladaptation of stroke survivors to self-care at home after hospital discharge is associated with complications, adverse events, high readmission rates to hospital, delayed recovery, psychological and emotional stress, social isolation and a low level of quality of life [5, 6]. Therefore, hospital to home transition care for this patient population has become a priority care area to optimize care outcomes and relieve burdens on the healthcare system [17]. Health coaching is an effective strategy to enhance transition care for stroke survivors and their caregivers. In this study, we adapt the definition of health coaching by Wolever and colleagues described as “a patient-centered approach wherein patients at least partially determine their goals, use self-discovery or active learning processes together with content education to work toward their goals, and self-monitor behaviors to increase accountability, all within the context of an interpersonal relationship with a coach” [18]. Although considerable evidence supports the effectiveness of health coaching on quality of life and activities of daily living in other chronic diseases [19–23], findings from the mentioned studies indicate that the effect on stroke survivor’s health outcomes varies.

The aim of this study is to determine the effectiveness of nurse-led health coaching for stroke survivors and primary caregivers in hospital to home transition care in Chongqing, China. We hypothesis that stroke survivors in the health coaching intervention group will demonstrate better health outcomes at 12 weeks from the baseline compared to the usual care group.

## Methods/design

### Study design

This is a single-blind, two-arm parallel randomized controlled trial of a nurse-led health coaching program for stroke survivors versus routine care situated in the First Affiliated Hospital and the Third Affiliated Hospital of Army Medical University in Chongqing, China (Fig. 1). These hospitals are chosen as they are nearly identical regarding patient population and staff profiles. They serve for the same civilian population in a large metropolitan area and are administered by a similar governance body, policies, standards; and have same staffing levels and education and training for staff. The intervention will last 12 weeks. Data collection will be at three time points: the baseline (after the consent form is signed), immediately after the intervention (at 12 weeks), and 24 weeks from the baseline. Stroke survivor-caregiver dyads will participate in the study and will be recruited from the hospitals mentioned above. Four stroke wards from these tertiary hospitals (two from each hospital) will participate in the study. The care services provided to stroke patients in these wards are similar. The nurse-led health coaching program will be conducted at stage 1 in the hospital and stage 2 in the community after discharge from hospital. The trial follows the Recommendations for Intervention Trials (SPIRIT) that is presented in Additional file 1.

**Fig. 1 Fig1:**
[figure not shown]
Flow chart of study design

### Ethical approvals and consent to participant

The protocol was approved by the Southern Adelaide Clinical Human Research Ethics Committee (Approval Number: 230.18) and the Institutional Review Boards of the First Affiliated Hospital and the Third Affiliated Hospital of the Army Medical University, China. Informed consent will be obtained from all participants. Any information provided by participants will be collected in a de-identifiable form. Each participant and participating health facility will be given a unique numerical code to represent them on data collection forms used throughout the project. Any information provided to the study will be treated in strict confidence, and none of the participants will be individually identifiable in research reports. All paper-based questionnaire surveys and patients and caregivers files will be locked in a safe cabinet in the research office and only the co-investigator will have access to it.

### Eligibility: Inclusion criteria and exclusion criteria

#### Inclusion criteria and exclusion criteria for stroke survivors

Participants will meet all of these inclusion criteria: (1) aged 18 or over; (2) first-time stroke survivors (ischemic or haemorrhagic stroke); (3) will be discharged to home-care setting within a week; (4) have no cognitive impairment (Montreal cognitive assessment score ≥ 23) [24]; (5) not participating in other clinical trials at the same time; (6) can speak Chinese without aphasic; and (7) willing to participate in this study.

Participants will be excluded if they have (1) comorbidities such as severe circulation, digestive, immune, blood and endocrine systems disorders; (2) existing cerebrovascular disease with impaired limb function; (3) mental illness (such as Panic disorder, PTSD, Psychosis, Schizoaffective disorder, Schizophrenia); or (4) existing cognitive impairment (depression and delirium) and disabilities prior to stroke .

#### Inclusion criteria and exclusion criteria for caregivers

Caregivers will meet all these inclusion criteria: (1) aged 18 or over; and (2) be the primary caregiver. Caregivers will be excluded if they (1) are under 18 years old; or (2) have mental or cognitive disabilities.

#### Inclusion criteria for health coaches

Health coaches will be trained intervention nurses from each participating ward of the two hospitals, and they will conduct all interventions in this study. The eligibility criteria for health coaches are (1) a registered nurse; (2) at least a bachelor’s degree in nursing; and (3) at least 5-years work experience in the care of stroke survivors.

### Randomization

We will allocate eligible participant dyads to the intervention group or the control group using simple randomization, with an equal allocation ratio of 1:1, using IBM SPSS Statistics version 25 random sampling and allocation methods. A research associate who is not involved in recruitment, intervention allocation or outcome assessment will generate the random numbers. Allocation concealment will be ensured by the research associate putting the group allocation into sequentially numbered, opaque, sealed envelopes to inform the intervention nurse after baseline data collection for each dyad.

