### Sample size

The sample size is estimated on the basis of the primary outcome, stroke survivors’ self-efficacy, measured by the SSEQ [27]. We generated the estimated effect size of 0.5 based on a 7.5 point between-group change in SSEQ from baseline reported in a similar RCT by Lo et al. [42]. We also estimated a pooled SD of 6.42 based on the 95% confidence interval of the SSEQ score reported in the study. A type I error of alpha 0.05 and a power of 80% were used in the sample size calculation. We expect a 10% dropout rate. Therefore, we will require 70 dyads per treatment group. In total, we will recruit at least 140 participant dyads into the study.

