### Data analysis

The intention-to-treat (ITT) approach will be adopted for data analysis. Statistical analysis will be performed using IBM SPSS Statistics version 25 and STATA software version 15. The normality of data will be assessed using normality plots. Percentages will be presented to summarise category data. Means and standard deviation, or medians and IQR, will be presented to describe countinous data with normal distribution and non-normal distribution respectively. Two group comparisons of demographic and clinical characteristics at baseline will be performed using Chi-square tests for category data and independent t-tests or non-parametric Mann-Whitney U-tests for data with normal distribution or non-normal distribution respectively.

The researcher will determine changes in outcome measures at baseline, and 12-week and 24-week follow-ups. To estimate mean changes over time in primary and secondary outcomes, linear mixed effect models for repeated measures will be used to assess differences between the two groups. Fixed effects in the model will include time, group, covariate(s) and the two-way interaction of group and time. The model will also include participant-level random effects to account for correlation between participants’ repeated measures over time. Value and confounders that include age, gender, educational level, insurance type, and number of comorbidities at baseline will be adjusted in this model. A *p* < 0.05 will be regarded as statistically significant for all statistical tests. Estimated mean differences, including 95% confidence intervals and *p*-values, will be reported for (time × group) interaction effects.

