### Quality control

Prior to commencing the project, the researcher ([name]) will introduce the intervention study to each participating ward through a one-hour presentation. The purpose of the presentation is to inform health professionals about the study, gain their support and allow them to ask questions in relation to the study.

Four intervention nurses from participating wards (one from each ward) will participate in two workshops (two hours each) to standardize health coaching interventions throughout the project. The workshops will enable intervention nurses to practice health coaching skills, gain feedback from the researcher and their peers, and ask any questions they may have. The workshops will be provided by the researcher ([name]) who is a qualified academic member of the Nursing College of Chongqing Medical University and a specialist in chronic disease management including the care of stroke survivors. Intervention nurses will also be provided with written “Health Coaching Intervention Program Guidelines” (Table 1).

The researcher ([name]) will recruit 3–5 hospital volunteers (laypersons) for a workshop to test whether they understand the questionnaires and measure the time taken to complete. Each intervention nurse will undertake a pilot coaching activity with workshop volunteers and receive feedback from the researcher. To ensure data quality, double data entry will be conducted by four master’s students who are not involved in this study.

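### Allocation is not balanced within the four wards and ward is not in the named model; adding ward as a covariate is a cheap gain in precision, not a correction of bias.

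*Protocol article*

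**What the plan says.** The protocol article fixes the allocation method under Randomization: "We will allocate eligible participant dyads to the intervention group or the control group using simple randomization, with an equal allocation ratio of 1:1". It names no blocks and no stratification by ward or hospital. The Abstract gives the target: "the estimated sample size is 140 (70 in each group".

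Under Study design, recruitment is from four stroke wards, two in each of two hospitals. That section describes the hospitals as almost alike in patients and staff, and care in the wards as similar. Quality control describes the coaches: "Four intervention nurses from participating wards (one from each ward". The criteria for health coaches say that these nurses deliver the whole intervention, and Usual care gives the control arm to other nurses.

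The Data analysis section names the terms of a mixed model for repeated measures: "Fixed effects in the model will include time, group, covariate(s) and the two-way interaction of group and time". Random effects are at participant level. The covariates named are age, gender, education, insurance type and number of comorbidities, with wording that appears to add the baseline value. Ward, hospital and coach do not appear.

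**The concern.** Ward is known for every dyad before randomisation. It may carry differences in case mix and discharge practice that bear on the outcome. Simple randomisation can leave a ward with clearly more dyads in one arm than in the other, and the stated model has no term to take such differences out.

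Two things follow. The estimate contains a chance component due to ward that could have been removed, and the residual variance contains whatever part of the outcome wards explain. Both show up as a wider confidence interval than necessary. The stake is efficiency and the interpretability of the realised sample, not the validity of the test.

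**Working it through.** **1. The plan's own figure.** The inputs are in the Sample size section: "A type I error of alpha 0.05 and a power of 80% were used in the sample size calculation"; a standardised effect of 0.5 ("We generated the estimated effect size of 0.5 based on a 7.5 point between-group change in SSEQ from baseline"); and "We expect a 10% dropout rate". A two-sided test is assumed because the sidedness is not stated.

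- n per group = 2(1.960 + 0.842)² / 0.5² = 62.8, rounded up to 63.
- With dropout: 63 / 0.9 = 70. The planned 70 per group reproduces.
- Power with 63 analysed per group: Φ(0.5 / √(2/63) − 1.96) = 80.1%.

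The effect of 0.5 is used below because it is the value that gives 70. The same section also says "We also estimated a pooled SD of 6.42", and 7.5 / 6.42 = 1.17, which is not 0.5. That discrepancy is a separate matter and does not enter this point.

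**2. Group totals under simple randomisation.** The size of an arm is Binomial(140, 0.5).

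- P(exactly 70/70) = 6.7%.
- Central 95% range for one arm: 58 to 82.
- Power with 10% loss is Φ(0.5 / √(1/(0.9a) + 1/(0.9b)) − 1.96):

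| Split a/b | Power |
|---|---|
| 70/70 | 80.1% |
| 65/75 | 79.9% |
| 60/80 | 79.3% |
| 58/82 | 79.0% |

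Averaged over all splits, power is 79.8%. The unequal totals hardly matter.

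**3. Splits within wards.** The article gives no ward sizes. Equal wards are assumed, 140 / 4 = 35 dyads each, so an arm within a ward is Binomial(35, 0.5).

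- 13/22 or worse: 0.1755 in one ward; 1 − (1 − 0.1755)⁴ = 54% for at least one of four.
- 12/23 or worse: 0.0895 in one ward; 1 − (1 − 0.0895)⁴ = 31% for at least one of four.

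A noticeable imbalance in some ward is therefore quite likely. These are frequencies of splits, not effects on the estimate.

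**4. What adjustment would gain.** Let ρ be the share of the variance of the analysed outcome that lies between wards. The article gives no value, so a range is assumed. Adjusted power is Φ(0.5 / √((1 − ρ) × 2/63) − 1.96), ignoring the few degrees of freedom spent:

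| Assumed ρ | Power with ward in the model | Gain over 80.1% |
|---|---|---|
| 0.01 | 80.5% | 0.4 points |
| 0.02 | 80.9% | 0.8 points |
| 0.05 | 82.1% | 2.0 points |
| 0.10 | 84.1% | 4.0 points |

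**5. Which ward effect counts.** The result to be reported is the group-by-time interaction. If baseline is one of the repeated responses, a ward difference that is constant over time cancels from change since baseline, and a plain ward main effect does nothing for that contrast. Only ward differences in change remain. So ρ refers to the change, or to the baseline-adjusted 12-week outcome, and not to the raw score.

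**The case against.** The strongest reply is that nothing here is invalid. Under simple randomisation an unstratified comparison is unbiased, and its standard error already allows for chance imbalance between wards. That stands. A reader might infer from the ward splits that ward differences bias the treatment effect; the article does not support this, because the splits are random error that the confidence interval covers.

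Second, the article calls the wards and hospitals alike, and the repeated-measures contrast already removes constant ward differences. Both make a large gain less likely and favour the lower part of the assumed range. But the similarity is asserted without data, and it neither balances nor adjusts anything.

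Third, ward could be added in an analysis plan that is not shown, and the article's covariate wording is open. This is fair, and it means that adding ward contradicts nothing. Still, five other covariates are named and ward is not.

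Fourth, stratified blocking is tempting but not clearly better here. According to Recruitment, the unblinded intervention nurse checks eligibility, takes consent and opens the envelopes. With one such nurse per ward, she would see the whole past sequence of her ward's blocks, and keeping the list elsewhere would not prevent that. Simple randomisation is the least predictable choice in this setting. Trial status also expected recruitment to end on 10 October 2019, while the protocol version is dated 20 January 2020, so few or no dyads may remain to be randomised.

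**Conclusion.** The point holds as a modest, inexpensive improvement. Arms are not balanced within wards by design, and the named model omits a structural factor known for everyone. Including it would gain about 0.4 to 4 power points if wards explain 1% to 10% of the variance of the analysed outcome. That range is an assumption; the article gives no ward variance.

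Two stronger conclusions do not follow. One is that failing to reach exactly 70 per group weakens the trial: an exact 70/70 is indeed unlikely, but within the 95% range the cost is at most 80.1 − 79.0 = 1.1 power points. The other is that a ward term settles the one-coach-per-ward structure. Coaches act only in the intervention arm, so a coach effect is a ward-by-group effect. A ward main effect or a ward-by-time term leaves it in place, and its size depends on an intraclass correlation that the article does not give.

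**What to change.** Before unblinded data are seen, add ward (four levels) as a fixed effect in the primary model, in one of two forms that reach the 12-week contrast:

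- model the 12- and 24-week responses, with the baseline value as a covariate and ward as a main effect; or
- keep baseline among the responses and include ward and ward by time.

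The first form costs 4 − 1 = 3 parameters. The second costs 3 + 3 × 2 = 9 with three time points. Either is affordable with about 126 dyads analysed (140 × 0.9).

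State in the same place that this adjustment does not remove coach effects in the intervention arm. Describe the group sizes as about 70 each, which is a change of wording only. No change to the randomisation method is asked for.

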### Evaluator blinding

Participant dyads and intervention nurses will not be blinded due to the nature of the intervention. However, the researcher, who will collect the outcome assessments and undertake data entry and analysis, will remain blinded to treatment allocations. Intervention nurses, who will conduct the telephone and outpatient clinic follow-ups, will not be blinded as they will need to update participant information and maintain the intervention and service.

### Description of the interventions

Interventions that will be implemented in this study are based on effective health coaching components identified in a systematic review and meta-analysis conducted by the research team prior to this RCT study and other systematic reviews and studies on health coaching in chronic condition management [20, 22, 25, 26]. A two-stage intervention for the intervention group will be conducted as described in the following.

### Stage I: Interventions while in hospital

An intervention nurse will provide participant dyads with individualized health coaching within one week prior to discharge from hospital.

Individualized health coaching: intervention nurses will provide participant dyads with two face-to-face individualized health coaching sessions (20–30 min each). All health coaching sessions will be based on the “Health Coaching Intervention Program Guide” (Table 1) to standardize interventions in the study.

**Table 1 Tab1:** The guide for health coaching intervention program

Health coaching session	Items	Topics
Three days prior to discharge	Self-care skills	To demonstrate the skills of personal hygiene, dressing, eating, maintaining continence and transferring, and how to record health coaching diary for self-monitoring.
	Creating a safe home environment	To assess the home environment according to the stroke survivors’ needs. To demonstrate and discuss how to create a safe home environment. Examples will be provided in relation to the increase of the lighting in the living room, bedroom and toilet. Minimizing the furniture and provide the patient with an accessible area. Creating floor with non-slip, no steps, and to install handrails on the walls.
	Functional ability rehabilitation and exercise plan	Based on the plan provided by medical specialist, the coach will demonstrate how to perform the recommended activities, provide opportunity for stroke survivors to perform these activities and gain feedback from the coach. The training also includes, but not limited to: • Maintain the correct posture and correct the abnormal pattern. • Maintain the functional position of the paralysed limb to prevent malformation. • Active and passive function training on hemiplegic side. • Guide the transfer training, swallowing function training.
Two days prior to discharge	Medication management	• Give health education about medication use, monitoring side effects and medication adherence. • Demonstrate how to record the medication using Health Coaching Diary.
	Complication prevention	• To assess the complication prevention according to the stroke survivors’ condition. • To demonstrate how to prevent, identify and manage stroke-related complications(second stroke, bedsore, falls and urinary tract infection).

Sources: 1. Stroke Foundation. National Stroke Audit – Rehabilitation Services Report 2016. Melbourne, Australia. 2. National Stroke Foundation. Clinical Guidelines for Stroke Management 2010. Melbourne, Australia. 3. https://strokefoundation.org.au/

Outline of health coaching activities:
Participant dyads will establish their transition care goals and develop personal action plans.An intervention nurse will demonstrate self-care and other skills required by participant dyads when providing Activities of Daily Living (ADLs) and Instrumental Activities of Daily Living (IADL) and participating in social engagements.Participant dyads will discuss a safe home environment including safe toileting, walking and sleeping. Home environment modifications will be undertaken prior to discharge when needed.An individualized functional recovery and physical exercise plan will be developed based on the recommendation from the stroke survivor’s medical specialist. An intervention nurse will discuss the plan and demonstrate skills when appropriate. The functional recovery and physical exercise plan will be recorded in the “Stroke Health Coaching Diary” (Additional file 2).Stroke survivors will be given an individualized treatment and rehabilitation plan provided by medical specialists, have opportunities to discuss and clarify the plan and receive medication education from an intervention nurse. The treatment and rehabilitation plan will be recorded in the “Stroke Health Coaching Diary”.An intervention nurse will demonstrate how to prevent, identify and manage stroke-related complications.

